**Figure 1. F1:**
[figure not shown]
Graphical representation of the multistate model. Notation: Subcohort: [*C*_*1*_; care states (*S*_*1*_,...,*S*_*15*_); discontinuation of care: *D*; SUD remission state: *R*; terminal states: (*T*_1_,...,*T_4_*); *t*: time, *p*: probability] The 3 dots connecting the states indicate that the depicted relationships are possible for the other states not shown in this figure. p: probability; SUD: substance use disorder; t: time.

We will adopt a semi-Markov assumption [59] under which transition intensities depend on only the duration that patients spend time in the current state before transitioning. This framework allows transition intensities to vary over time rather than assuming constant transition intensities as in the Markov framework. Time is defined as the duration since entry into a state, with the clock reset to 0 upon entry into the cohort and each subsequent state. At any time since entry into the initial state, a patient occupies 1 of the 21 states (17 transient states and 4 terminal states). Movements between states *j* and *k*
$\left(j,k=S_{1},\ldots ,S_{15},D,R,T_{1},\ldots ,T_{4}\right)$, are governed by a 21-by-21 matrix of transition intensities $q_{jk}(t,z(t))$, which is a function of time *t* and covariates z(t). Intensities capture the instantaneous probability of moving from state *j* to *k*.

Under the semi-Markov assumption, we will fit separate flexible parametric survival models [60,61] for each transition:

$\log\{q_{jk}(t,z(t))\}=s(\log(t)|\eta ,k_{0})+\beta^{T}z_{i}(t)$.

For simplicity, we omit transition-specific subscripts for the parameters $\left(\eta ,k_{0},\beta \right)$. In the model, $s(\log(t)|\eta ,k_{0})=\sum_{i=1}^{k_{0}}\eta_{i}B_{i}(\log(t))$ represents the log cumulative baseline intensity function, which we model flexibly using restricted cubic spline basis functions (also known as natural cubic splines) $B_{i}(\cdot )$, with corresponding coefficients $\eta_{i}$. The number of knots, $k_{0}$, determines the number of basis functions and thus the flexibility of the baseline intensity functions. For covariates *z*_*i*_(*t*), the coefficients β represent the log hazard ratios at time t. The unknown parameters to be estimated or selected from data are $\left(\eta ,k_{0},\beta \right)$. We will use the Akaike information criterion based on data to select the number of knots, with lower Akaike information criterion values indicating better model fit. The regression coefficient parameters (η,β) will be estimated by using the maximum likelihood approach for statistical inference [62,63]. For each transition, we will include prespecified covariates for adjustment when the number of transitions allows (at least 10 transition events per covariate), and if additional covariate selection is required, variables that are statistically significant at the 5% level based on Wald tests will be included [64]. The estimated transition intensities are transformed to a transition probability from states j to k at time t since entry into state j at time s (s<t, s and *t*>0), by integrating, $p_{jk}(s,t)=\exp\left\{-\int_{s}^{t}q_{jk}(u,z(u))\;du\right\}$.

Multiple incident SUD events may be observed within the same patient (see Quantitative Study Population). For example, a patient may have an incident SUD event, eventually experience a terminal state such as ceasing SUD care (eg, one who receives no SUD care for 194 days), and then experience a second incident SUD event. Including multiple incident events from the same patient within the same subcohort in the MSM framework may introduce within-patient correlation and reflect care pathways that differ from those of the initial episode. We will account for within-patient correlation using a sandwich variance estimator for the parameter estimates. The number of prior incident events will be included as a covariate or used as a stratification factor, depending on its distribution.

To assess model adequacy, we will compare spline-based estimates of the cumulative baseline hazard with nonparametric estimates derived from the Kaplan-Meier method for visual agreement. To evaluate the proportional hazards (time-independent effects) assumption, we will test for time-dependent effects by including interactions between covariates and spline functions of time. If these interaction terms are not statistically significant at the 5% level, they will be excluded from the final model.

Additionally, we assume that transition times are exactly observed. Lastly, it is assumed that the distribution of health care visit times is independent of transition probabilities for simplicity (noninformative visiting process). We will primarily use the R (R Foundation) package *flexsurv* to implement the MSMs and develop our own modules to transform the fitted results to answer research questions.

We will consider sensitivity analyses if sample size and other feasibility constraints permit. This includes stratified analyses by subgroups defined by the number of outpatient visits (eg, patients with more visits may have poorer health) [65,66] or clinically meaningful periods. For instance, impactful operational changes occurred due to COVID-19 mitigation restrictions (eg, reduced in-person care), so we will consider estimating models before, during, and after these restrictions were in place. Additionally, stratified analyses by SUD type will be considered to acknowledge that each substance may sometimes require unique forms of care, such as pharmacotherapy usage.

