**Objective:**

This study protocol describes research that will comprehensively characterize the pathways of care used by those who obtain care for SUD and compare the quality and outcomes associated with these care pathways. Specific aims are to (1) apply multistate models (MSM) to characterize the spectrum of care transitions among patients with SUD within a large integrated health system, (2) generate data-driven insights to improve care delivery for SUD using estimated MSMs, and (3) observe and explore patient and clinician experiences with care transitions across common care pathways using qualitative methods.

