### States for the MSMs

States will capture 3 types of events related to SUD care: initial states, transient states, and terminal states. Defining states requires a balance of specificity to produce actionable information, and parsimony to allow for an estimable statistical model with accurate estimates and smaller SEs.

Initial states in the MSMs represent the clinical settings that triggered an incident event at the start of an SUD care episode, corresponding to the 5 subcohorts in Table 1.

There are 3 types of transient states. The first type is care states, which include different types of care provided in the health care system to treat the SUD, defined by combinations of setting and service type (Table 2). We opted to define 15 preliminary SUD care states based on a combination of 3 settings and 5 service types. The second type of transient state is temporary discontinuation of care. Entry into the temporary discontinuation care state is triggered using a clinically meaningful threshold for time elapsed between SUD treatment visits. The last transient state is SUD remission, which represents an improvement in the patients’ disease.

**Table 2. T2:** Transient states and terminal states are represented in the multistate models.

Category	States included	Description
Transient states	A total of 17 transient states include 15 care states derived from crossing 5 service types with 3 care settings; temporary discontinuation of SUD^a^ care; and remission of use disorder.	Care states Service types Evaluation and assessment Behavioral treatment and counseling Prevention, education, and case management Pharmacotherapy Other service Settings Outpatient Intensive outpatient Inpatient or residential Other transient states Discontinuation of SUD care A lack of SUD care over a specified period^b^ Remission of use disorder Low risk score on alcohol and substance use screen; clinically meaningful reduction on screening scores or <2 symptoms on *DSM-5*^c^ checklist; SUD remission diagnosis
Terminal states	4 states representing the end of a care episode	Death, derived from dates in health care enrollment records or Washington State death data Loss to follow-up, defined as at least 31 days without KPWA insurance coverages Ceased SUD care (no medication fills or services with a qualifying SUD diagnosis for more than 194 days Administrative censoring (in the middle of a care episode when data collection ends)

a SUD: substance use disorder.

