b Temporary discontinuation will be defined separately for each care state using an appropriate threshold for time elapsed between visits that reflects acceptable gaps in care for that specific state. All of these periods will be shorter than 194 days to distinguish temporary discontinuation from ceasing substance use disorder care.

c *DSM-5*: *Diagnostic and Statistical Manual of Mental Disorders, Fifth Edition*.

Terminal states indicate the end of an SUD care episode (Table 2), such as ceasing SUD care.

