#### Aim 2. Generate Data-Driven Insights to Improve Care Delivery Using Estimated MSMs

We will apply the estimated MSM parameters from aim 1 to generate inferences that yield actionable data-driven insights to improve care delivery for SUD. As shown in Table 3, these inferences fall into three general categories: (1) examine SUD care states and terminal event rates, (2) identify empirically common care pathways, and (3) identify the extent to which guideline-concordant care is achieved.

**Table 3. T3:** Summary of inferences from the multistate model and how they could be used by health systems to improve care for SUD^a^.

Key questions	Relevance to health systems	Analytic goal		
		Examine care states and terminal event rates	Identifies empirically common care pathways	Measure guideline-concordant care
How does the accessibility of reaching each care state vary?	Informs whether types of care are being reached at an expected rate, and whether resources are needed to support a given care type	✓		
How does the probability of occupying care states and terminal states vary over time?	Informs timing of interventions to address challenges in the delivery of SUD care	✓		
What are inefficient sequences of care following each initial state over time?	Identifies services or care patterns that need greater coordination (eg, multiple evaluations with delayed pharmacotherapy)		✓	
What is the contribution of each care state in achieving terminal states?	Prioritize SUD care types and inform places where specific SUD services are best delivered	✓		
What are the common (ie, most probable) sequences of SUD care following each initial state?	Helps health systems anticipate the needs of patients with SUD		✓	
How often and where is guideline-concordant care achieved?	Identifies care processes and locations to target for quality improvement			✓
How does the probability of occupying terminal states differ across patient subgroups?	Provides insights into whether outcomes differ for specific groups of patients who have incident SUD events in each setting	✓		
How do answers for the above key questions differ across patient characteristics?	Informs whether approaches to improve SUD care delivery should be tailored to different patient subgroups.	✓	✓	✓

a SUD: substance use disorder.

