#### Aim 3. Observe and Explore Patient and Clinician Experiences With Care Transitions Across Common Care Pathways Using Qualitative Research Methods

Aim 3 includes observations and interviews to explore the context for SUD care decisions and experiences with SUD care transitions. We will perform direct observations [74,75] of patient-clinician encounters during salient SUD visits, such as behavioral health intake visits. Witnessing and documenting these interactions will provide key information on decision-making regarding various clinical scenarios. We will also conduct semistructured in-depth interviews with a broad sample of patients and clinicians to collect views, preferences, and needs of individuals engaged in different care pathways. Observations and interviews will be concurrent to inform ongoing data collection and confirm data sufficiency [76]. We will draw on phenomenological [77] and ethnographic theory [78] to explore emic [79], or insider perspectives on care transitions.

The quantitative and qualitative components synergize in 2 ways: first, by using an explanatory sequential sampling mixed methods design [80] whereby qualitative interview participants are purposely sampled from potentially meaningfully rich subgroups of patients who have embarked on specific care pathways identified in the quantitative population. Second, by integrating quantitative and qualitative data in the analysis phase. Specifically, we will reapply the inclusion criteria for aims 1 and 2 to identify patients who were recently identified to start an episode of SUD care at the time of qualitative data collection. We will then match the patient’s observed sequence of care to model-identified pathways estimated in aim 1. We will then purposively sample [81] patients from six pathways: (1) two of the overall most common care pathways, (2) two of the most common care pathways that contain guideline-concordant care, and (3) two of the most common care pathways that have a high probability of reaching negative terminal states (eg, death). We will be open to the emergence of other important care patterns to guide our sample selection, and we may consider other important factors, such as SUD type and/or severity, when defining these groups. We will sample approximately 3‐5 patients from each pathway (estimated to be 35 patients) and ensure representation across demographic groups and those with different SUD types.

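### One temporary-discontinuation state with a reset clock cannot represent entry thresholds that differ by care state, so exits to ceased care are mistimed and the outputs built on them biased

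*Protocol article*

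**What the plan says.** - **Dependence.** Statistical Analyses, Aim 1, adopts a semi-Markov model in which "transition intensities depend on only the duration that patients spend time in the current state before transitioning". The model equation adds covariates z(t). Time is measured "with the clock reset to 0 upon entry into the cohort and each subsequent state".
- **States.** Table 2 (States for the MSMs): "A total of 17 transient states include 15 care states derived from crossing 5 service types with 3 care settings", plus one state for temporary discontinuation (D) and one for remission (R).
- **Entry to D.** Table 2, footnote b: "Temporary discontinuation will be defined separately for each care state using an appropriate threshold for time elapsed between visits". Every threshold is to be shorter than 194 days.
- **Ceased care.** Table 2 makes this a terminal state, reached after more than 194 days without a medication fill or a qualifying SUD service.
- **History.** The only history term named is the number of prior incident events, which concerns earlier episodes. No named covariate records the states visited earlier in the current episode or the care state left on entry to D. The model checks described cover baseline fit and proportional hazards.
- **Use.** The Objective is to "compare the quality and outcomes associated with these care pathways". Table 3 asks "What is the contribution of each care state in achieving terminal states", and Aim 2 answers with restricted mean survival times (RMSTs) from each care state to each terminal state. Aim 2 also computes probabilities of whole sequences, including cycling between care and discontinuation. Aim 3 samples two of its six pathways for their high probability of a negative terminal state.

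**The concern.** Three definitions do not fit together: an entry threshold for D that varies by care state, a ceasing rule fixed at 194 days, and one D state whose clock starts at zero for everyone. Because every threshold is below 194 days, a patient who meets the ceasing rule from a care state has already crossed into D. The time left until ceasing is then fixed by which care state was left. The model discards exactly that information: both the origin and the time since last service are lost on entry to D.

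Ceased care is one of the four terminal states and the one used in the worked RMST example (Table 5). Care-state-specific ceasing probabilities, RMSTs to ceasing and the probabilities of sequences passing through D all inherit the error. A difference between two care states could then reflect the chosen gap thresholds and their pooling instead of retention in care.

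A wider point sits behind this. Given the current state, time in it, covariates and entry setting, the model gives the same future whatever care came earlier in the episode. That equality is assumed, not estimated.

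**Working it through.** **1. The plan's own count.** 5 service types × 3 settings = 15 care states; 15 + D + R = 17 transient states; 17 + 4 terminal = 21. This agrees with Aim 1 and confirms a single D.

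**2. Time from D to ceased care.** I assume that D is entered when its threshold g is reached and that the 194 days run from the last service. Then time in D before ceasing is about 194 − g. The article gives no thresholds, so g is assumed:

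| Assumed g (days) | 194 − g (days) |
|---|---|
| 30 | 164 |
| 60 | 134 |
| 90 | 104 |
| 120 | 74 |

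**3. What one D implies.** Pool origins with g = 30 and g = 120. Exits to ceased care then occur at 74 and at 164 days after entry, and the model applies both to everyone in D.
- 30-day origin: some predicted ceasing at 30 + 74 = 104 days without service, before the rule allows it.
- 120-day origin: some predicted ceasing at 120 + 164 = 284 days, long after the rule would have applied.

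Any unequal thresholds produce this conflict. Only its size depends on the assumed values.

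**4. Chance of ceasing once in D.** Assume a constant return-to-care rate of 0.005 per day, no other exits and equal inflow from the two origins.
- g = 30: exp(−0.005 × 164) = exp(−0.82) = 0.440
- g = 120: exp(−0.005 × 74) = exp(−0.37) = 0.691
- Pooled D: (0.440 + 0.691)/2 = 0.566 for both

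**5. Direction of the bias, counted from the last service.**
- *Hiding a difference.* If the same share p of patients reaches D from each origin, the true chances of ceasing are 0.44p and 0.69p. Pooling gives 0.57p for both.
- *Creating one.* If the 0.005 rate also holds before D, the true chance is exp(−0.005 × 194) = exp(−0.97) = 0.38 for both. Pooling gives exp(−0.15) × 0.566 = 0.49 for the 30-day origin and exp(−0.60) × 0.566 = 0.31 for the 120-day origin, a false gap of about 18 points.

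**6. RMST horizons.** The earliest ceasing that pooling can produce is the shorter threshold plus (194 − the longer one), here 104 days after last service. An RMST is affected only if its horizon goes beyond that point. The 90-day column of Table 5 would be reached if two thresholds differ by more than 194 − 90 = 104 days, or if spline smoothing moves exits earlier. Longer horizons are affected at smaller differences.

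**7. What the model can still separate.** Take a small chain with assumed one-step probabilities: A to B 0.30, D 0.65, death 0.05; B to A 0.20, D 0.75, death 0.05; D to A 0.25, B 0.25, ceased 0.48, death 0.02. The eventual chance of ceasing is 0.900 from D whether the patient came from A or B, but 0.838 starting in A and 0.843 starting in B. Earlier history is lost at D; the state occupied still matters.

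**The case against.** The strongest reply is that the semi-Markov assumption is declared and referenced, the study calls itself exploratory, and the plan weighs specificity of states against parsimony. Intensities also depend on z(t), which includes time-varying SUD-related conditions such as nonfatal overdose. Models are fitted separately for five entry settings. New states may be added where frequent enough. Multimedia Appendix 2, not shown, deals with sequence probabilities. All of this stands, and it makes the general lack of memory a limit on interpretation, not an error.

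It does not answer the conflict at D. Covariates on patient condition do not carry the originating threshold. The plan's example of a new state is concurrent care, not a split of D. Calculations from the fitted model cannot restore information that the model omits.

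A reader might infer that comparing pathway outcomes is impossible, or that ranking pathways reduces to ranking their last states. The documents do not support either. Death and loss to follow-up do not depend on the care-gap rule and can occur from any state visited, and pathways through different states or entry settings can differ in predicted outcome. Nor does pooling always pull care states toward an average: step 5 shows it can do the opposite. D is also not shown to be the only route to ceasing, since the article does not say that a patient in remission must pass through D first.

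The effect on Aim 3 is modest. Two of the six pathways use negative-outcome probability, sampling is purposive, and the team stays open to other care patterns.

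**Conclusion.** The handling of D is wrong as written. Care-state-specific thresholds, a fixed 194-day rule and one clock-reset D cannot all be represented together. Exits from D to ceased care, and the ceasing probabilities, longer-horizon RMSTs and sequence probabilities that use them, are distorted whenever thresholds differ. The bias may hide real differences or create false ones.

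The size cannot be fixed from the article. The 0.57 in place of 0.44 and 0.69, and the 0.49 and 0.31 in place of 0.38, rest on assumed thresholds of 30 and 120 days, a return rate of 0.005 per day and equal inflow. The conclusion also assumes that D and ceased care are dated when their thresholds are crossed and that the 194 days run from the last service. That is the natural reading, but the hypothetical Figure 2, where ceasing rises through day 15, does not fit it, so the dating rule should be stated.

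More generally, the model cannot detect effects of earlier care within an episode, given the current state, time in it, covariates and entry setting. This weakens the pathway comparison without making the objective unattainable.

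**What to change.** **For exits from D (needed before fitting).** State how entry to D and ceased care are dated. Then do one of the following:
- Run the clock from the last service, with delayed entry at the threshold. Ceasing then falls at the same clock time for every origin, and what is modelled is return to care and the other exits up to that day.
- Split D, or stratify its exit models, by a few groups of originating care states that share a threshold.

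A single proportional-hazards term for origin on the reset clock is not enough. It rescales the hazard and cannot shift the time of exit.

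**For the general assumption.** Where events allow, add previous state or originating group as a covariate and test it. Where they do not, say that pathway comparisons rest on the assumption that earlier care has no effect given the current state.

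**Cost.** No new data, but a few more parameters or strata, limited by the plan's events-per-covariate rule. Three origin groups entered as a covariate need two indicators, so 2 × 40 = 80 events for a transition (20 under the permissive rule of 10). A full split by origin would give 15 + 15 + 1 = 31 transient and 35 total states, and at least 15 × 40 = 600 events for the D states (150 under the permissive rule) in each subcohort model. Grouping is therefore the practical choice.

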Table 4 summarizes estimates that can be obtained from fitted MSMs to generate our inferences and answer additional research questions. We will calculate point estimates and CIs and further characterize variation in output quantities across states graphically.

**Table 4. T4:** Summary of multistate model output quantities.

Output	Description	Example question answered
Intensity matrix	Instantaneous probability of moving from 1 state to another	How likely is a transition from an initial primary care state to a behavioral treatment and counseling care state over a small incremental unit of time?
Transition probability matrix	Probability of moving from 1 state to another over a specific time duration	What is the probability of moving from an initial primary care state to a behavioral treatment and counseling care state within 14 days of SUD^a^ identification?
Hitting probability	Point estimate of the probability of ever reaching a state	What is the probability of ever reaching pharmacotherapy during a care episode?
Mean sojourn time	Mean length of time a patient stays in a state	On average, how long does a patient stay in the evaluation and assessment care state before transitioning to another state?
Restricted mean transition-free time	Mean length of time a patient spends in transient states before reaching a terminal state	What is the average time before a patient ceases SUD care after receiving pharmacotherapy?
Expected first passage time	Expected days until hitting a specific state of a set of states	How long until a patient receives SUD pharmacotherapy?
Expected number of visits	Expected number of times a state is reached between 2 given times	What is the predicted number of times behavioral treatment and counseling are reached in the first 30 days of a care episode?
Survival plot	Probability of not reaching a state, as a function of time	How is the probability of not ceasing SUD care after their index SUD event?

a SUD: substance use disorder.

How does the accessibility of each state vary? We will use the models to describe how the accessibility of each state varies by estimating the dynamics of transitioning between different types of care for SUD. We will report and characterize variation in (1) transition probabilities, (2) hitting probabilities, (3) mean sojourn time, (4) expected first passage time, and (5) expected number of visits (definitions in Table 4).

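### The printed transition-probability formula gives the chance of not making the j-to-k move; coded as printed, it would make the measures built on transition probabilities wrong

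*Protocol article*

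**What the plan says.** All of the following stands in the Protocol article, under Statistical Analyses.

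- **Meaning of q_jk (Aim 1).** "Intensities capture the instantaneous probability of moving from state *j* to *k". It belongs to a single move, not to leaving state j in general.
- **Conversion (Aim 1).** "The estimated transition intensities are transformed to a transition probability from states j to k at time t since entry into state j". The printed expression is p_jk(s,t) = exp{−∫ from s to t of q_jk(u,z(u)) du}.
- **Model equation (Aim 1).** The left-hand side is log q_jk, the log intensity. The right-hand side is a spline in log time plus covariate effects. The text then says that the spline "represents the log cumulative baseline intensity function, which we model flexibly using restricted cubic spline basis functions".
- **State space (Aim 1).** "At any time since entry into the initial state, a patient occupies 1 of the 21 states (17 transient states and 4 terminal states". The index for j and k runs over the 15 care states, discontinuation, remission and the four terminal states. Moves among the transient states go both ways.
- **Definition (Table 4).** The transition probability matrix is described thus: "Probability of moving from 1 state to another over a specific time duration". The probability of not reaching a state is a separate entry in the same table, the survival plot.
- **Use.** Study Outcomes derives the probability of guideline-concordant care from estimated transition probabilities. Aim 2 applies this to follow-up within 7 and 30 days of an emergency department visit, starting from the initial state.
- **Software (Aim 1).** flexsurv is named for the models, but the team will "develop our own modules to transform the fitted results to answer research questions".

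**The concern.** A transition probability from j to k should start at 0 for k different from j and should rise when the intensity towards k rises. It should also account for patients who leave j for somewhere else. The printed expression does none of these things. It has the form of a survival function for one cause of exit, labelled as a probability of moving.

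The conversion is left to modules that the team will write, and this is the only conversion formula in the text. If it is implemented as printed, a care state that patients seldom reach would be reported as highly accessible, and a follow-up measure would fall as follow-up improved. Health systems are meant to act on these figures.

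Two nearby statements need correcting at the same time because they feed the same step. The model equation and the description of its spline disagree on whether the modelled quantity is an intensity or a cumulative intensity. The state index also leaves out the initial state, from which several of the planned probabilities start.

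**Working it through.** **Inputs.** The formula, the meaning of q_jk, the 21 states (so up to 20 destinations from a transient state) and the definitions in Table 4 come from the protocol. The protocol gives no numerical intensities and no numerical result to reproduce. All rates below are assumed, per day.

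**Step 1: properties that need no assumed rates.** For the printed exp{−∫q_jk}:

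- at t = s it equals exp(0) = 1, although nobody has moved;
- for an impossible move (q_jk = 0) it equals 1 at all times;
- it falls as q_jk or elapsed time rises;
- no other exit from j appears in it, so the values over k, with the probability of staying, have no reason to sum to 1.

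**Step 2: the quantity needed for a first move.** With Q_jl(u) the cumulative intensity from j to l, and u the time since entry into j, the probability that the first exit from j is to k and occurs by t is

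F_jk(t) = ∫₀ᵗ exp{−Σ_l Q_jl(u)} q_jk(u) du.

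For constant rates this is (q_jk / q_j)·(1 − exp(−q_j t)), with q_j the sum of all exit rates.

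**Step 3: three exits, 0.05, 0.02 and 0.01, over 14 days.** Here q_j = 0.08 and q_j t = 1.12. The probability of staying is exp(−1.12) = 0.326, and 1 − 0.326 = 0.674.

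| Rate | Printed formula | First-move probability | 1 − printed |
|---|---|---|---|
| 0.05 | exp(−0.70) = 0.497 | 0.625 × 0.674 = 0.421 | 0.503 |
| 0.02 | exp(−0.28) = 0.756 | 0.250 × 0.674 = 0.168 | 0.244 |
| 0.01 | exp(−0.14) = 0.869 | 0.125 × 0.674 = 0.084 | 0.131 |
| Sum | 2.12 | 0.674 (1.000 with staying) | 0.878 (1.204 with staying) |

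The order of destinations is reversed. Taking 1 minus the printed value restores the order, but the values remain too high because competing exits are still ignored.

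**Step 4: range of assumed rates, 30 days, competing exits 0.03 and 0.01.**

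| Target rate | Printed | First-move probability |
|---|---|---|
| 0.005 | 0.861 | 0.082 |
| 0.02 | 0.549 | 0.278 |
| 0.10 | 0.050 | 0.704 |

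With 20 equal exits of 0.01 at 30 days, the printed value is 0.741 each (sum 14.8), 1 minus it is 0.259, and the first-move value is 0.050.

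One case used time-varying Weibull intensities: target scale 40 and shape 0.7; competitors with scale 25, shape 1.3 and scale 100, shape 1. At 7, 14 and 30 days the printed values fall (0.744, 0.619, 0.441), while the first-move probabilities rise (0.234, 0.317, 0.383). The two can come close at one time point, but they move in opposite directions.

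**Step 5: returns and indirect routes.** Take the middle row of Step 4. Add moves in both directions between the target and the 0.03 state at 0.02, and from each of them to the terminal state at 0.01. The probability of occupying the target at 30 days is then 0.259, against 0.549 from the printed formula.

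**Step 6: the two linked statements.** The equation has log q_jk on the left, while the text calls the spline a log cumulative intensity; both cannot hold. The model check later in Aim 1 compares spline-based cumulative hazards with nonparametric ones, which points to the cumulative reading. Separately, the index and the count of 21 (17 + 4) leave no place for the initial state. Yet Table 4's 14-day example and the emergency department measures start from it.

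**The case against.** The strongest reply is that this is a misprinted equation, not a planned wrong analysis. Table 4 describes the right quantity in words and keeps the probability of not reaching a state apart. The planned stacked occupancy plot would visibly fail if bands summed to 2 or more. An established package is named for the models. All of this is fair, and no code is shown. It makes the consequence conditional, but the printed formula remains wrong and nothing in the article corrects it.

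Three stronger readings are tempting, and the protocol does not support them.

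- **That every Aim 2 output is wrong.** Only guideline-concordant care is explicitly tied to transition probabilities. Sequence probabilities, and with them the pathway ranking and Aim 3 sampling, are said to come from the fitted models, with details in an appendix not shown. Restricted mean survival time is defined as an area under a terminal-event-free curve, and the terminal-state comparison across subgroups is descriptive. Neither is said to use this formula.
- **That the spline mismatch causes a double integration.** That would require fitting on one scale and reading on the other, which no passage says. The planned check against nonparametric estimates should also expose a scale error.
- **That measures starting from the initial state cannot be computed.** The text defines initial states, has patients enter one and starts the clock there. The omission is in the index and the matrix dimension.

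Nor is there a fault in the wording of the follow-up measures: they already ask about transitions within a stated number of days.

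**Conclusion.** The point stands in a limited form. The expression printed as the j-to-k transition probability is the cause-specific probability of not having made that move. It contains neither competing exits nor indirect routes, and it contradicts Table 4. This follows from the formula and the definition of q_jk alone.

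The consequence is conditional. If the team's modules implement the formula as printed, Table 4's transition probabilities and the guideline-concordant care measures computed from them, including 7- and 30-day emergency department follow-up, would be wrong, and destinations from a given state would be ranked in reverse. Other Aim 2 outputs are affected only if they are computed through this formula. Fitted intensities and hazard ratios do not pass through it.

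The sizes rest on assumed rates. In the 14-day example the error runs from 0.50 against 0.42 for the commonest move to 0.87 against 0.08 for the rarest. The spline description and the initial-state index are consistency corrections, and no numerical effect is claimed for them.

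**What to change.** 1. Replace the printed formula. For first moves, state the cumulative incidence ∫ exp{−Σ_l Q_jl(u)} q_jk(u) du, with all exits from j in the survival term. For multi-step occupancy and for having reached a state by day t, state that the quantity is obtained by simulation or convolution from all fitted semi-Markov transition models. Taking 1 minus the present expression is not enough.
2. Reconcile the model equation with its description. If the spline is the log cumulative intensity, as the text and the planned model check indicate, put log Q_jk on the left-hand side and obtain q_jk by differentiation.
3. Add the initial state to the state index and to the intensity matrix, since Table 4 and the emergency department measures need transition probabilities from it.

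The cost is three corrected statements and a check of any conversion code already written against them. A useful test for that code is that, for every starting state and time, the first-move probabilities and the probability of staying sum to 1. No new data are needed, and final quantitative data collection is not expected until November 2027.
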